### Exclusion criteria

(1) Patients with severe cardiovascular and cerebrovascular diseases, including but not limited to myocardial infarction, stroke, and severe arrhythmias; (2) Patients with significant organ failure, such as end-stage renal disease requiring dialysis, or liver failure requiring transplantation; (3) Patients with contraindications to vertebral augmentation surgery, such as coagulopathy or anticoagulant therapy that cannot be safely managed; (4) Patients with skin ulceration, infection, or rash around the puncture point that would increase the risk of complications during surgery; (5) Patients requiring open surgery for their OVCF, as this may indicate a more complex or severe fracture that could affect the study outcomes; (6) Patients who are unable to cooperate with surgery due to cognitive impairment, psychiatric illness, or other reasons that would make the procedure unsafe or unsuccessful; (7) Patients with a history of pathological fractures, indicating underlying bone disease or malignancy.

### Inclusion criteria for the control group

(1) Diagnosed elderly patients (aged 60 years and older) with OVCF who underwent vertebral augmentation and did not experience refracture within a specified follow-up period after the initial surgery; (2) Elderly patients aged 60 years and older with a bone mineral density T-score of -2.5 or lower, indicating osteoporosis.

### Exclusion criteria for the control group

(1) Patients who underwent vertebral augmentation due to a pathological fracture caused by underlying bone disease or malignancy; (2) Elderly patients with OVCF receiving conservative treatment only, without undergoing vertebral augmentation surgery.

### Survey contents and methods (observation indicators)

The study includes eight categories of observation indicators and a total of 541 data items, as follows:Basic information: 21 data items, including age, gender, BMI, etc.Habit characteristics: 34 items in total, including eating habits, exercise habits, family activities, medication, and behavioral risk factors.Past medical history: 13 data items.Comorbidities/medication: 29 items.Diagnostic tests: 253 data items, including routine blood tests, coagulation tests, biochemistry, bone metabolism, sex hormones, white blood cell count, skin, pancreas and serum tests, thyroid function tests, tumor markers, imaging, functional score, color Doppler ultrasound, echocardiography, electrocardiogram, sarcopenia, infection index, and SF-36 quality of life (Table S1 and S2).Treatment plan: 36 data items.Postoperative follow-up: 139 data items, including follow-up table, functional score, bone metabolism, and SF-36 quality of life.Adverse events: 16 data items.

The follow-up plan includes two parts:

Patients will enter the data independently using their mobile phones, with real-time network supervision to ensure accurate data entry.Doctors will conduct monthly or regular telephone follow-ups to guide postoperative rehabilitation, which will last for 1 year.

The clinical data of all OVCF patients will be collected and input into a structured database through an established clinical research platform (Table 1). The platform will classify and manage the data into eight categories: basic information, habit characteristics, past medical history, comorbidities and medication, diagnostic examination, treatment plan, postoperative follow-up (Table S3), and adverse events. The data will be collected from the hospital, including medical history, physical examination, hematology, and imaging data, were directly uploaded through photos, and the research platform staff sorted the data into the corresponding categories. The data collected outside the hospital will be uploaded through a two-dimensional code automatic real-time clocking method, and the doctors supervised the data entry, which will be then sorted by the research platform staff. To analyze bone formation and resorption markers, blood samples will be analyzed using laboratory techniques such as ELISA to measure the levels of specific markers associated with bone metabolism. The results will be interpreted by comparing the marker levels to established reference ranges or normal values, aiding in the assessment of bone health and related conditions.

**Table 1 Tab1:** Schedule of enrolment and assessments

	**Treatment stage**	**Pre-operation examination**	**One year after the operation**
Patient information	+		
Eating habits	+		
Exercise habit	+		
Family activities	+		
Medication	+		
Behavioral risk factors	+		
Routine blood test		+	
Seven items of blood coagulation test		+	
Biochemistry test		+	
Four items of bone metabolism test		+	+
Six items of sex hormone test		+	
Interleukin-Growth Hormone-Cortisol-Insulin-Serum		+	
Seven items of thyroid function		+	
Imaging examination		+	
Function score		+	+
Colour ultrasonic diagnosis		+	
Echocardiogram		+	
Sarcopenia		+	
Electrocardiogram		+	
Tumor marker		+	
Infection indicators		+	
SF-36 life quality		+	+
Follow-up table			+

For the whole-genome microarray genotyping data, we will use the Infinium Asian Screening Array + MultiDisease -24 (ASA-MD) genotyping chip. Genome Studio software will be used for quality control of raw data. Samples with a call rate less than 99% and SNPs with a call rate less than 98% will be filtered out. After quality control, PLINK software will be used for further processing. Samples with kinship will be excluded by calculating the Identity-By-Descent (IBD) and inbreeding coefficient (F). Imputation and preprocessing will be performed based on the 1000 genomes of the East Asian population and the Han population genome of the previous study. SNPs that do not meet the Hardy–Weinberg equilibrium (HWE ≥ 0.001) and minor allele frequency (MAF ≥ 0.01) will be excluded.

For the genome-wide methylation beadchip data, DNA from vertebral and peripheral blood samples stored at -80 °C will be bisulfite converted, and the Infinium MethylationEPIC BeadChips (Illumina) will be used for genome-wide DNA methylation profiling. BeadChips will be processed according to the manufacturer’s protocol, and then imaged using the iScan Microarray Scanner (Illumina). The resulting idat files will be processed using the CHAMP Bioconductor package. Samples with missing probes greater than 10% and probes missing in samples more than 20% will be removed, and KNN imputation will be carried out for the rest. Probes with less than three beads in more than 5% of samples and non-CpG, cross-reactive, or non-specific probes will also be removed. Probes mapping on the sex chromosomes and contained SNPs will also be removed. After checking sample outliers by MDS plots and beta values distribution of Type-I and Type-II, data normalization will be performed using BMIQ. Samples with genotype data will be kept, and methylation beta values will be transformed into M values.

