The objective of this study is to investigate the genetic and epigenetic markers associated with osteoporosis and bone mineral density, and their impact on refracture risk among elderly patients. We aim to collect vertebral body blood and peripheral blood samples from 500 patients with OVCF who will undergo detailed clinical assessments, genome-wide genotype and methylation profiling at baseline. Following the surgical intervention, these patients will be followed up for 1 year to monitor refracture events, during which clinical and genome-wide methylation data will be collected again. These valuable data will enable us to identify genetic and epigenetic markers that can predict OVCF and refracture risk in the elderly and develop accurate prediction models.

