### Biomarker identification and prediction analysis

The GWAS of bone mineral density will be carried out in PLINK using linear regression model, assuming an additive allele effect. Covariates for age, gender, drug usage and the first five principal components to account for residual population structure will be also included in the model. The genomic control inflation factor will be used to adjust the *p*-values. The adjusted *p*-values equal to or smaller than 5E − 8 will be considered as genoome-wide significant. We will conduct a GWAS using case–control design to invesgate the genetic variants associated with osteoporosis.

This study will use whole-genome methylation data from vertebral and peripheral blood samples of 500 osteoporosis patients with recurrent fractures after vertebral augmentation and 1000 natural population controls from the Chinese Academy of Sciences. To identify differentially methylated positions (DMPs) between patients with and with out refracture, we will perform an epigenome-wide association study (EWAS) and meQTL analysis. Patients with refracture who underwent vertebral augmentation will be selected as cases, and an equal number of patients without refracture will be selected as controls based on age range and epidemiological indicators such as BMI, disease, and medication history. We will analyze changes in methylation levels of osteoporosis- and bone mineral density-related sites in elderly patients with refracture within one year after surgery. The R language DMRfinder package will be used for analysis, and functional annotation of the identified DMPs and differentially methylated regions (DMRs) will be performed.

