### Clinical implications/impact of the study

The systematic analysis of molecular mechanisms underlying osteoporosis and bone mineral density phenotypes is of great importance, and this study aims to explore cross-omics molecular markers that affect these phenotypes based on multi-omics data and the degree of physiological aging. The research objectives of this study include:Conducting genome-wide association analysis and genome-wide epigenetic association analysis of osteoporosis and bone mineral density to identify genetic and epigenetic molecular markers related to these phenotypes and to deeply analyze their molecular mechanisms.Evaluating the feasibility of DNA methylation in assessing the effect of postoperative intervention for osteoporosis by analyzing changes in methylation levels of bone mineral density related sites in elderly patients with refracture after vertebral augmentation for OVCF within one year after surgery.Improving the risk prediction model of osteoporosis by considering multiple factors such as genetic variation and environmental factors, which can provide a scientific basis for the molecular classification and prevention of related diseases and serve as a paradigm for biomedical researchers conducting multi-omics life data research.

The results of this study can provide valuable insights into the molecular mechanisms of osteoporosis and bone mineral density phenotypes, which can facilitate the development of effective interventions and personalized treatments. The findings can also contribute to the establishment of a risk prediction model for osteoporosis that takes into account genetic and environmental factors, which can help identify individuals at high risk for developing osteoporosis and enable targeted preventive measures. Overall, this study has the potential to make significant contributions to the field of osteoporosis research and improve clinical practice in the management of related diseases.

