### Advanced features of this study

To ensure data quality, we have established a special OVCF real-world research database system that supports data operation traceability, automatic logical verification, and other functions based on the ALCOA principle.We have assigned a special person to inspect the organization and implementation of the study, verify the data, and ensure accurate, timely, and complete data collection through quality control and assurance work meetings attended by all implementation units.To control the risk of loss to follow-up, we have implemented a patient data entry method and set up a special person to supervise the data entry. Follow-up personnel (doctors/nurses) will also follow up on patients’ data entry by monthly or regular telephone follow-up.To control patient compliance bias, we have established a unified clinical research platform for observation indicators such as out-of-hospital medication and dietary habits, and jointly set up personalized anti-osteoporosis programs with the department of endocrinology, rehabilitation, and nutrition to increase patient compliance. The study protocol was designed as a real-world study, and the final analysis was divided into groups according to the completion of the protocol to make the results closer to the clinical situation and increase the credibility of the study.We have implemented strict biobank management, ensuring the samples were only used for this study, destroyed after research, and information leakage was strictly controlled.Our study utilizes a multi-omics approach, incorporating whole genome sequencing and genome-wide methylation analysis to explore the interaction between genetics, epigenetics, and the environment in osteoporosis and bone mineral density phenotypes. This provides a more comprehensive understanding of the molecular mechanisms underlying these conditions.We have included a control group of 1000 healthy individuals from the Chinese Academy of Sciences natural population cohort, providing a larger and more diverse sample for comparison and analysis.We are exploring the feasibility of DNA methylation as a tool for evaluating the effect of postoperative intervention for osteoporosis by analyzing changes in the methylation levels of bone mineral density-related sites in elderly patients with refracture after vertebral augmentation for OVCF within one year after surgery.We are improving the risk prediction model for osteoporosis by incorporating multiple factors such as genetic variation and environmental factors, providing a more personalized approach to prevention and treatment.Our study is conducted in multiple medical centers, increasing the diversity of patient populations and enhancing the generalizability of our findings.

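### The objective on assessing postoperative intervention rests on methylation change in refracture patients alone, with no response or comparison group named, although paired responses are scheduled

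*Protocol article*

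**What the plan says.** The second objective listed under Clinical implications/impact of the study is "Evaluating the feasibility of DNA methylation in assessing the effect of postoperative intervention for osteoporosis by analyzing changes in methylation levels" at BMD-related sites, in refracture patients over the year after surgery. Advanced features of this study and the Discussion repeat it.

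The matching analysis, under Biomarker identification and prediction analysis, is one sentence: "We will analyze changes in methylation levels of osteoporosis- and bone mineral density-related sites in elderly patients with refracture within one year after surgery".

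The data to be collected are wider than that sentence uses:

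- Background: "these patients will be followed up for 1 year to monitor refracture events, during which clinical and genome-wide methylation data will be collected again".
- Table 1 marks three measures both before operation and at one year: "Four items of bone metabolism test", function score and SF-36. The list of observation indicators agrees: "Postoperative follow-up: 139 data items, including follow-up table, functional score, bone metabolism, and SF-36 quality of life".
- On the bone markers, the text beside Table 1 says: "The results will be interpreted by comparing the marker levels to established reference ranges or normal values".

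Refracture status is used in a separate analysis: "To identify differentially methylated positions (DMPs) between patients with and with out refracture, we will perform an epigenome-wide association study (EWAS) and meQTL analysis".

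**The concern.** To judge whether a marker can assess an intervention, its change has to be set against something: a measured response, a treatment contrast or a group with a different course. The article states a population (patients with refracture) and a quantity (methylation change) and names nothing to set the change against.

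At stake is the claim that closes the Discussion, that the study shows methylation to have potential for evaluating how well postoperative intervention works. An analysis carried out as described could find clear methylation change and still give no evidence for that claim.

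**Working it through.** The point rests on no figure, so the check sets the parts of the Protocol article side by side.

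**1. What the stated analysis estimates.** Let ΔM be a patient's methylation change at a site (follow-up minus baseline), and let R = 1 for refracture and R = 0 for none. The sentence under Biomarker identification and prediction analysis estimates the mean of ΔM given R = 1. R is constant in that group, so refracture cannot act as the response. A non-zero mean could reflect the intervention, recovery from the index fracture and surgery, a new fracture between the two samples, or simply a year's passage. Nothing in the analysis separates these.

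**2. What the objective needs.** At least one of:

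- an association between ΔM and a within-patient response ΔY;
- the contrast of mean ΔM between R = 1 and R = 0;
- a contrast of ΔM between intervention groups.

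**3. Whether the article supplies any of these.**

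| Candidate | Where it appears | Linked to methylation change? |
|---|---|---|
| Four bone metabolism tests | Table 1, both times | No; the stated use is comparison with reference ranges |
| Function score | Table 1, both times | No |
| SF-36 | Table 1, both times | No |
| Refracture within one year | Background; EWAS with versus without refracture | Not as a contrast of change |
| Grouping by protocol completion | Advanced features: "the final analysis was divided into groups according to the completion of the protocol" | No |
| BMD change | No repeat imaging marked in Table 1 | No |

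Candidate responses exist. The missing element is the link from any of them to ΔM.

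**4. What the restriction to refracture patients sets aside.** The Background cites refracture rates of 6.2% to 51.8% after vertebroplasty. If the 500 patients are an unselected surgical cohort and those rates applied over the follow-up year (both assumptions), the stated population is 500 × 0.062 = 31 to 500 × 0.518 = 259 patients. Up to 500 − 31 = 469 to 500 − 259 = 241 others would have methylation collected again but would not enter this analysis. This is an illustration only. Elsewhere the article describes the 500 as patients with recurrent fracture, and the argument in steps 1 to 3 does not depend on the count.

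**The case against.** The strongest objection is scope. This is a condensed article, and the regression model for a secondary objective is commonly left to a full protocol or SAP. That stands for model detail, and the absence of a link can be asserted of this article only. It does not dispose of the point, because the article itself states the population and the quantity, and those two do not answer the objective.

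Three stronger readings are tempting, and the documents do not support them:

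- A reader might infer that the study has no response at all. It has several: bone markers, function score and SF-36 at both times, and refracture over the year.
- A reader might infer from the reference-range sentence that the markers will be analysed as normal or abnormal, and go on to calculate the information lost. The sentence describes how assay results are read clinically. It defines no analysis variable or responder rule and does not exclude continuous change. Loss figures would price an analysis that nobody has specified.
- A reader might infer from Table 1 that one-year BMD change is impossible. Table 1 marks imaging before operation only, but it also marks a follow-up table at one year, and Supplementary Table S3 is not shown. Later imaging cannot be excluded.

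It is also fair to say that adding bone markers does not isolate an intervention effect. No intervention contrast is described, and the baseline sample is taken around an acute fracture. This limits what may be concluded, but it does not defend an analysis with no response.

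**Conclusion.** The point holds in this form: the stated analysis can show that methylation at the chosen sites changed in refracture patients, but not that the change tracks any response. It therefore cannot support the conclusion drawn in the Discussion. The consequence is qualitative: one of the three listed objectives stays unanswered even with complete data. No power or efficiency figure applies.

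This assumes that the sentence under Biomarker identification and prediction analysis is the whole planned analysis for this objective, that the separate EWAS by refracture status is not a contrast of change (it is not described as one), and that no unseen document supplies the link. The other objectives are not affected.

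**What to change.** Under Biomarker identification and prediction analysis:

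1. Define the population as all patients with paired methylation samples, with and without refracture.
2. Regress peripheral-blood methylation change at the pre-selected sites on the within-patient change in each of the four bone metabolism tests, kept continuous and adjusted for baseline level: ΔM = a + b·log(marker at one year / marker at baseline) + c·(baseline marker level). The coefficient b is the quantity of interest.
3. Compare methylation change between patients with and without refracture.

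Beside Table 1, say that reference ranges serve clinical description only. In Clinical implications, Advanced features and the Discussion, limit the conclusion to association between methylation change and these responses.

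Cost: some added analysis, including a multiplicity rule that covers four markers per site. The marker tests are already scheduled at both times and methylation is already to be collected again, so no visit is added. The regression assumes that the second methylation sample is taken close to the one-year marker test, which the article should confirm. The acute fracture may affect the baseline marker level, and this should be stated as a limitation.

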### Biomarker identification and prediction analysis

The GWAS of bone mineral density will be carried out in PLINK using linear regression model, assuming an additive allele effect. Covariates for age, gender, drug usage and the first five principal components to account for residual population structure will be also included in the model. The genomic control inflation factor will be used to adjust the *p*-values. The adjusted *p*-values equal to or smaller than 5E − 8 will be considered as genoome-wide significant. We will conduct a GWAS using case–control design to invesgate the genetic variants associated with osteoporosis.

This study will use whole-genome methylation data from vertebral and peripheral blood samples of 500 osteoporosis patients with recurrent fractures after vertebral augmentation and 1000 natural population controls from the Chinese Academy of Sciences. To identify differentially methylated positions (DMPs) between patients with and with out refracture, we will perform an epigenome-wide association study (EWAS) and meQTL analysis. Patients with refracture who underwent vertebral augmentation will be selected as cases, and an equal number of patients without refracture will be selected as controls based on age range and epidemiological indicators such as BMI, disease, and medication history. We will analyze changes in methylation levels of osteoporosis- and bone mineral density-related sites in elderly patients with refracture within one year after surgery. The R language DMRfinder package will be used for analysis, and functional annotation of the identified DMPs and differentially methylated regions (DMRs) will be performed.

To predict BMD and OVCF risk, we will use multiple linear regression and multiple logistic regression models, respectively. We will include sex and age as predictors along with independent BMD-related genetic variants identified in previous studies and methylation sites identified in this study. Fracture risk score will also be evaluated based on age, gender, bone mineral density (BMD), previous fracture history, family history, and other risk factors. Prediction accuracy will be estimated using the R-squared correlation (R2) for BMD and the area under the curve (AUC) for OVCF risk. Sensitivities and specificities will be calculated using confusion matrices, where the predicted probability greater than a certain threshold (t) will be considered the predicted shape type, and t will be optimized to maximize the sum of sensitivity and specificity.

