## Methods

### Recruitment of patients

This will be a prospective multicenter cohort study conducted in 5 medical centers, including Peking University International Hospital, Beijing Tiantan Hospital affiliated to Capital Medical University, Beijing Changping District Hospital, Tengzhou Central People’s Hospital, and Linfen People’s Hospital. The study was approved by the Biomedical Ethics Committee of Peking University International Hospital (batch number: 2022-KY-0010-01). Recruitment of elderly patients with OVCF after vertebral augmentation and those without refracture will take place from December 2022 to December 2023. All participants will provide informed consent. The flow chart is presented in Fig. 1. An example of refracture in elderly individuals with osteoporosis who undergo vertebral augmentation is shown in Fig. 2.

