### Sample size

The power of EWAS is essential for detecting differentially methylated positions (DMPs) between cases and controls. Similar to GWAS, the power of EWAS depends on four key factors, including study design, sample size, effect size, and burdon of multiple test correction. Previous simulation analysis has shown that a sample of 500 cases and 500 controls would achieve 80% power to detect differential methylation at epigenome-wide significance (*P* < 1E-6) with a methylation odds ratio of 1.28 or mean methylation differences of 5% in case–control designs of EWAS (cite the original pubication) [19]. Therefore, we aim to recruit 500 elderly patients with OVCF who underwent vertebral augmentation surgery, as well as 500 healthy controls matched for age, gender, and race from the CAS cohort who did not develop OVCF or osteoporosis. This sample size will provide adequate statistical power for detecting significant differences in DNA methylation levels between cases and controls and enable us to identify epigenetic markers associated with refracture after vertebral augmentation surgery for OVCF.

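### The bone mineral density GWAS lists its covariates but omits centre, although patients come from five hospitals: a minor, cheap gain in precision is left unused

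*Protocol article*

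**What the plan says.** Under Biomarker identification and prediction analysis, the article specifies the model: "The GWAS of bone mineral density will be carried out in PLINK using linear regression model, assuming an additive allele effect". The adjustment set follows: "Covariates for age, gender, drug usage and the first five principal components to account for residual population structure". The p-values are then corrected ("The genomic control inflation factor will be used to adjust the" p-values), and adjusted values of 5E-8 or below "will be considered as genoome-wide significant".

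Under Recruitment of patients: "This will be a prospective multicenter cohort study conducted in 5 medical centers". Under Advanced features of this study, the multicentre design is presented as a strength: "Our study is conducted in multiple medical centers, increasing the diversity of patient populations".

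Centre, site or scanner does not appear anywhere as a covariate, stratum or random effect. The article also does not describe how BMD is made comparable across hospitals.

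**The concern.** An unseen analysis plan may add detail, but the article already states this model's covariate list, so the list can be judged as written. It leaves out a factor that the design itself creates. The article gives the purpose of the principal components as residual population structure. They are therefore aimed at ancestry, not at differences between hospitals in BMD measurement or in the severity of the patients they operate on.

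If hospitals differ in mean BMD, the difference enters the residual variance and widens every SNP standard error. A second possibility is confounding: if allele frequencies also differ by hospital, part of a hospital difference in BMD can appear as a SNP effect. The first mechanism needs only a BMD difference between hospitals. The second needs both differences together.

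**Working it through.** **The plan's own figure.** The article gives no power calculation for the BMD GWAS. Its only one is for the EWAS: "a sample of 500 cases and 500 controls would achieve 80% power to detect differential methylation at epigenome-wide significance", at P < 1E-6, for a mean methylation difference of 5%. No standard deviation is given. Solving the two-sample formula for it gives SD = 0.05 / [(4.892 + 0.842) × √(2/500)] = 0.05 / 0.3626 ≈ 0.138. The stated 500 per group can thus be matched only by choosing that SD, and it does not bear on centre adjustment in the BMD model.

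**Inputs.** From the article: five centres, about 500 patients, additive linear regression, threshold 5E-8. Assumed, because the documents do not give it: the share *s* of BMD variance due to centre after the listed covariates, taken as 2%, 5%, 10% and 20%.

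**Precision.** For a SNP unrelated to centre:
- standard-error ratio, adjusted to unadjusted = √(1 − s)
- equivalent gain in sample size = 1/(1 − s) − 1

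**Power at 5E-8.** One-degree-of-freedom test, critical chi-square 29.72, N = 500. Non-centrality is N·r/(1 − r), where r is the share of within-centre variance explained by the variant. Without a centre term, r becomes r(1 − s). The benchmark is a variant with 80% power when centre is adjusted for, which needs r ≈ 7.3%. For s = 20%, non-centrality falls from about 39.6 to about 31.2.

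| s | SE ratio | SE reduction | Equivalent extra patients | Benchmark power without centre |
|---|---|---|---|---|
| 2% | 0.990 | 1.0% | 2% | 78% |
| 5% | 0.975 | 2.5% | 5% | 75% |
| 10% | 0.949 | 5.1% | 11% | 69% |
| 20% | 0.894 | 10.6% | 25% | 55% |

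The cost is four degrees of freedom, 4/500 = 0.8% of the information. At s = 2% the net gain is therefore only about 2.0% − 0.8% = 1.2%.

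**A variant of typical size.** The Background section reports that 20 genes together explained 5% of phenotypic variation, on average 5%/20 = 0.25% each. With N = 500 and s = 20%, power at 5E-8 for r = 0.25% is about 7E-6 with centre and 4E-6 without. For r = 1% it is about 0.0007 and 0.0003.

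**False positives.** Null SNPs were simulated for 500 patients in five equal centres, with no principal components and no genomic control. Mean chi-square without a centre term, by assumed genetic differentiation between centres (Fst):

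| Fst | s = 2% | s = 5% | s = 10% | s = 20% |
|---|---|---|---|---|
| 0 | 1.002 | 1.007 | 1.005 | 1.011 |
| 0.001 | 1.007 | 1.013 | 1.017 | 1.040 |
| 0.003 | 1.009 | 1.036 | 1.057 | 1.125 |

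With centre in the model it lies between 0.996 and 1.008. Inflation is visible only where both assumed quantities are at the high end, and before either of the plan's own safeguards is applied.

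**The case against.** The strongest reply is that the omission changes almost nothing in this GWAS. The centre share is assumed, and its lower half moves the standard error by 1% to 2.5%. The larger power losses apply to a variant explaining about 7.3% of variance, more than the 5% that the Background attributes to 20 genes together. For realistic variants, power is negligible either way. This stands, and it sets the priority.

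The second reply is that the plan already guards against confounding. The principal components absorb much of any allele-frequency difference that follows ancestry, and genomic control lowers average inflation. This also stands. A reader might infer that leaving out centre biases the SNP results, but the documents do not support more than a remote possibility. What the reply does not answer is precision: genomic control rescales test statistics and does not remove between-hospital variance.

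The third reply is that the article never says BMD is measured locally or on different devices. It says only that hospital imaging data are uploaded. Local measurement is plausible, but it is an assumption here.

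Two further extensions are tempting and should be resisted. One is to charge the refracture EWAS with the same omission. The article gives no regression covariates for that analysis, only an open-ended set of factors for choosing controls, so nothing stated there is wrong on this point. The other is to add centre to the BMD prediction model. Hospital coefficients cannot be applied to a patient treated elsewhere, and they would credit hospital differences to the reported R².

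**Conclusion.** The point holds for the BMD GWAS among patients, as a minor one. The stated covariate list omits centre in a five-hospital study. If centre accounts for 2% to 20% of BMD variance, adjusting would reduce the standard error by about 1% to 11%, worth about 2% to 25% more patients before the 0.8% cost in degrees of freedom. That range is an assumption, as is any hospital difference in BMD level or measurement. If hospitals do not differ, there is nothing to gain.

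The effect on detection at 5E-8 with about 500 patients is small, and SNP confounding is probably small after principal components and genomic control. The omission does not make the planned analysis invalid.

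**What to change.** - Add centre as a fixed effect (four indicators) to the covariates of the BMD GWAS among the fracture patients. The cost is four degrees of freedom in about 500. The recruiting hospital is not itemised in the article's data list, but the design makes it known for every patient, so no new data are needed.
- State who enters the BMD GWAS. If natural-population controls are included, run the centre-adjusted model in patients only. No control belongs to a hospital, so a hospital term cannot separate case status from data source.
- State how BMD is made comparable across hospitals, if it is.
- As a suggestion only: in the patient-only refracture EWAS, add centre to the factors used to select patients without refracture.
- Do not enter centre indicators as predictors in the BMD prediction model.
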